
### Participant timeline {13}

The flowchart of the time schedule, interventions, assessments and visits for participants is shown in Fig. 2.

**Fig. 2 Fig2:**
[figure not shown]
Flowchart of the patient flow through the trial. Displaying the differences between control and intervention groups and the screening instrument used at different measuring points

### Sample size {14}

In earlier studies of elderly frail patients undergoing colorectal surgery, 90-day mortality has been reported between 5 and 20% in the frail group and 0–7% in the non-frail group [6, 13]. One-year mortality has been reported to be above 20% in the frail group and up to 10% in the non-frail group [6, 14]. To prove a 10% absolute reduction in 90-day mortality from 15 to 5% in the intervention group, 170 patients must be included in each group (power 80% and significance level of 0.05). The expected loss to follow-up is 5% which has been compensated for in the sample size.

### Recruitment {15}

The intention is to include 340 patients, 170 in the intervention group and 170 in the control group. All patients aged ≥ 70 with a recently diagnosed cancer of the colon or rectum, available for curatively intended surgery, are recognized at the weekly MDT. At their next-coming appointment at the outpatient clinic, they are screened for frailty using the CFS-9 instrument. Thereafter, they receive verbal and written information regarding the study and are offered inclusion if they meet all inclusion criteria and no exclusion criteria. The recruitment of patients is on-going, and at present, approximately 50 patients have been included in the trial. The inclusion rate has been lower than anticipated, and we assume this is partly due to the COVID-19 pandemic and its impact on the workload for the health care staff and patients’ care seeking behaviours. As the trial moves forward and further centres are added, we predict the inclusion rate will increase. We assume the recruitment period will continue for another 2 years.

Since all patients undergoing surgery for colorectal cancer are discussed at MDT in accordance with the Swedish standardized care procedures for colorectal cancer, we will be able to identify all eligible patients and continue with frailty screening.

## Assignment of interventions: allocation

### Sequence generation {16a}

The allocation sequence is generated by the project leader manually in blocks of 10 (intervention/control). The envelopes are mixed, then numbered and drawn in numerical order as patients are included. The randomization is stratified for colon or rectal cancer.

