### Trial design {8}

The study is a prospective, randomized, multicentre superiority trial conducted at departments of surgery performing colorectal cancer surgery in an ERAS setting, in Sweden. Patients will be randomized into two parallel groups: control and intervention. The patients in the intervention group will be treated according to CGA and care preoperatively by geriatric, nursing, physiotherapist and dietician assessments followed by targeted and individualized interventions. The patients in the control group will be handled according to conventional preoperative assessments by anaesthesiologist and standard ERAS care. The groups will be stratified for colon or rectal cancer.

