### Concealment mechanism {16b}

Patients are randomized to the control or intervention group. The randomization is performed in the outpatient clinic, using sequentially numbered, thick, opaque sealed envelopes.

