### Implementation {16c}

Enrolment of participants is made by the surgeon. Assignment of participants to interventions is made by a study nurse or local principal investigator.

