## Assignment of interventions: blinding

### Who will be blinded {17a}

Neither participants nor caregivers are blinded to group assignment, as the intervention will be apparent. However, results will be analysed without knowledge of details of the groups.

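### Hand-made allocation in one fixed, published block size of 10, not stratified by centre, leaves an open-label trial exposed either to guessable assignments or to imbalance within hospitals

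*Protocol article*

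**What the plan says.** All statements come from the protocol article.

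- **Generation** (Sequence generation {16a}): "The allocation sequence is generated by the project leader manually in blocks of 10 (intervention/control". On the envelopes: "The envelopes are mixed, then numbered and drawn in numerical order as patients are included".
- **Strata** (same section): "The randomization is stratified for colon or rectal cancer". Trial design {8} agrees: "The groups will be stratified for colon or rectal cancer". Centre is not named as a stratum in either place.
- **Concealment** (Concealment mechanism {16b}): "The randomization is performed in the outpatient clinic, using sequentially numbered, thick, opaque sealed envelopes".
- **Roles** (Implementation {16c}): the surgeon enrols. "Assignment of participants to interventions is made by a study nurse or local principal investigator".
- **Blinding** (Who will be blinded {17a}): "Neither participants nor caregivers are blinded to group assignment, as the intervention will be apparent".
- **Centres** (Study setting {9}, Recruitment {15}): two centres take part and one to three more are being sought. About 50 of the planned 340 patients had been included.

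The article does not say whether each clinic holds its own envelope series or all hospitals draw from one. It also does not say whether envelopes are mixed within each block or across blocks.

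**The concern.** With a single block size that is known to everyone, the contents of a block are five cards of each arm. Staff who know what has been opened know what is left. Here the opened cards are visible: intervention patients are booked to a weekly intervention day and discussed at weekly team meetings, and the block size is published while most patients are still to be recruited.

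A guess can be acted on because entry involves judgement. Eligibility criteria {10} turn on a CFS-9 score of 4 to 8, an estimated life expectancy of at least 6 months and the ability to understand the study information. Whether and when to offer inclusion is also in the hands of clinic staff. If frailer patients were offered or deferred according to the expected arm, the arms would differ at baseline. An all-cause mortality endpoint protects against biased outcome assessment, but not against selection at entry.

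Leaving out centre matters in a different way. The Discussion concedes that routines may differ between hospitals, each centre supplies its own CGA team, and all levels of hospital are welcome. If blocks are not made within centre, nothing keeps the arms balanced inside a hospital.

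**Working it through.** The plan gives no figure of its own for predictability or centre balance. Its sample size does reproduce. For 15% vs 5%, 80% power and two-sided 0.05 (sidedness is assumed), the continuity-corrected formula gives 160 per group, and 160 / 0.95 = 168.4, so 169 against the stated 170. Nothing below changes that number.

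**1. Predictability if a clinic sees every earlier card in its block.** Inputs: block of 10, 1:1, so 5 cards per arm and C(10,5) = 252 equally likely orders.

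- *Best guess* (always name the arm with more cards left). Expected correct guesses with h = 5 per arm: h + ½ × (2^(2h) / C(2h,h) − 1) = 5 + ½ × (1024/252 − 1) = 6.53 of 10, or **65.3%**. An unpredictable sequence gives 50%.
- *Certain assignments.* Once one arm is used up, the rest of the block is known, so the number of certain cards is the length k of the final run. The number of orders with final run k is 2 × C(9−k, 4): 140, 70, 30, 10 and 2 for k = 1 to 5, which sum to 252. Mean = (140×1 + 70×2 + 30×3 + 10×4 + 2×5) / 252 = 420/252 = 1.67 of 10, or **16.7%**.

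For comparison, a fixed block of 4 gives 70.8% and 33.3%, so 10 is better than a small fixed block.

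**2. Predictability if hospitals share one series.** Each hospital sees only its own cards. By simulation, and generously letting staff know where blocks begin, a site with half the patients guesses about 57% correctly and a site with a quarter about 54%.

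**3. Balance within a centre if hospitals share one series.** Take a centre of m patients spread through the series, with 170:170 overall. A 60:40 or worse split means at most 0.4m or at least 0.6m in one arm.

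| m | Hypergeometric (170:170 fixed) | Binomial(m, ½) |
|---|---|---|
| 30 | 0.34 | 0.36 |
| 60 | 0.12 | 0.16 |

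**4. Balance within a centre if each clinic has its own blocks.** With blocks of 10 by tumour site and an assumed 67% colon share, the chance of a 60:40 or worse split is below 1% for 30 patients and essentially nil for 60.

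**Side by side:**

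| Arrangement | Best guess | 60:40 or worse, centre of 30 |
|---|---|---|
| Own series per clinic | up to 65% | below 1% |
| One shared series | about 54–57% | about 34% |

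**5. How little it takes to matter.** The planned rates imply 0.15 × 170 = 25.5 and 0.05 × 170 = 8.5 deaths. With 25 control deaths in 170, Fisher's exact test gives p = 0.035 for 12 intervention deaths and p = 0.057 for 13. Near the significance boundary, one death moves the conclusion.

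**The case against.** The article describes real safeguards. The envelopes are sequentially numbered, thick, opaque and sealed. They are mixed before numbering, so the shuffle sets the order and the project leader does not choose it. The enrolling surgeon is not the person who assigns. Candidates are identified at the weekly MDT and eligible patients who decline are logged, which makes selective inclusion easier to detect. These points stand, but none of them stops staff counting cards already opened.

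The 65% figure is a ceiling. It needs someone who tracks two parallel tumour-site series without error, and bias needs that person to act on the guess. Mixing across blocks would lower predictability, though it would also undo the blocking. This stands, and the figures are given as upper bounds for that reason.

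Several stronger readings are tempting and are not supported:

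- *Both harms at full strength.* The side-by-side table shows that each needs the arrangement that largely removes the other. Physical envelopes opened in the clinic make local series the likelier arrangement, but the text does not settle it.
- *The project leader recruits patients.* The article does not say so. It only fails to say that the person generating the list is outside recruitment.
- *Chance imbalance between hospitals is confounding.* Under valid randomisation it costs some precision and is covered by the type I error rate.
- *The primary analysis fails to adjust for centre.* Adjusted analyses are planned, and the choice of covariates may sit in an analysis plan that is not shown.

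**Conclusion.** The point holds as a weakness that is cheap to remove; it does not show that bias has occurred. Manual generation by the project leader, one published block size, tumour site as the only stratum and an open-label design are all stated. If clinics hold their own series and track them by tumour site, at most 65% of assignments can be guessed and about 17% are certain. If one series is shared, best guesses fall to roughly 54–57% for sites with a quarter to half of the patients, but a centre of 30 has about a 1 in 3 chance of a 60:40 or worse split. One of these applies, and the article does not say which. The figures assume mixing within blocks, staff who know the block boundaries and, for the imbalance, a centre whose patients are spread through the series. The resulting bias in 90-day mortality cannot be quantified from the document.

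**What to change.** For all patients still to be randomised (340 − 50, about 290), replace the list with one that is:

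1. computer-generated;
2. built from randomly varying block sizes that are not disclosed to sites or published during recruitment;
3. generated separately for each centre and for colon and rectal cancer;
4. produced and held by someone who neither enrols nor assigns patients.

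State in the protocol how envelopes or assignments are issued to each clinic. With three to five centres and two tumour sites there would be 6 to 10 strata. Some blocks will be left incomplete at the end, which is a small price for a trial of this size.

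The cost is a short amendment and a new list or set of envelopes. There are no extra patients or visits, and the planned 340 does not change. Patients already allocated stay as they are. The change has to come during recruitment, because selection at entry cannot be undone afterwards.

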### Concealment mechanism {16b}

Patients are randomized to the control or intervention group. The randomization is performed in the outpatient clinic, using sequentially numbered, thick, opaque sealed envelopes.

### Implementation {16c}

Enrolment of participants is made by the surgeon. Assignment of participants to interventions is made by a study nurse or local principal investigator.

## Assignment of interventions: blinding

### Who will be blinded {17a}

Neither participants nor caregivers are blinded to group assignment, as the intervention will be apparent. However, results will be analysed without knowledge of details of the groups.

### Procedure for unblinding if needed {17b}

Not applicable, there is no blinding.

## Data collection and management

### Plans for assessment and collection of outcomes {18a}

Data regarding the following outcomes: length of hospital stay and total number of hospital days, discharge destination, 30-day readmission rates, ADL performance, safe medication assessment and medication lists, CFS-9 score, postoperative complications and HRQoL are documented on the CRFs at baseline and at the postoperative visit. Data regarding mortality at 3 and 12 months will be collected and documented separately. Data needed for the health economical calculations and cost-effectiveness analysis; health care costs at 2 months and 12 months, HRQoL at baseline, 2 and 12 months follow-up and mortality data at 2 and 12 months will be collected and documented separately. A more detailed description of the data collection and the study instruments, along with their reliability and validity, are found under the “Outcomes {12}” section. The CRFs used for the control versus intervention group, in English versions, are attached to this article as Additional files 3 and 4.

### Plans to promote participant retention and complete follow-up {18b}

See items 11b and 11c. The follow-up in the study is performed at the same time as the postoperative follow-up regarding the cancer disease. Participants who choose to discontinue their participation in the trial will be registered in a log and no further measurements or registrations will be made. Participants who deviate from the protocol or fail to appear at follow-up will be checked against the mortality registry but not further registered.

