### Outcomes {12}

Primary endpoint:All-cause 90-day mortality

Secondary endpoints:Length of hospital stay and the total number of hospital days within 3 months after dischargeDischarge destination (home or nursing facility) and use of home help services30-day readmission ratesADL performance at follow-up in comparison to baselineSafe medication assessment at follow-up in comparison to baseline, adverse drug reactions (ADRs), underuse of evidence-based drug therapy and effects of inappropriate medications (analysed retrospectively)CFS-9 score at follow-up in comparison to baselinePostoperative complications according to the Clavien-Dindo scale at follow-upHealth-related quality of life (HRQoL) at follow-up in comparison to baselineCost-effectiveness based on mortality and HRQoL data (quality-adjusted life years [QALYs]) and costs of hospital care and primary care at baseline, 2 and 12 months post-surgeryAll-cause 1-year mortality

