#### Outcomes and measurements

*Hospital stays and discharge destination*, data regarding the length of hospital stay, total number of hospital days within 3 months after discharge, discharge destination and use of home help services and 30-day readmission rates for all participants is collected from patient medical records.*Dependence*, evaluation of the level of independence/dependence in an elderly individual is of great importance for example when establishing the need of home help services or other assistance. This is assessed using the activities of daily living (ADL)-staircase, which is a validated and commonly used instrument. The screening results in a score from 0 to 9, where 0 is completely independent and 9 is completely dependent [42, 43]. A clinically significant change is defined as a change of minimum 1 step in any direction on the ADL-staircase. ADL-function is assessed at baseline and at post-op visit (approximately 2 months post-surgery). The patients are assessed by a physiotherapist or a study nurse at baseline and follow-up.*Physical function*, the physiotherapists are also using hand grip strength (HGS) and six-minute walk test (6MWT) to make an overall assessment of the patient’s physical status to establish individual recommendations on physical activity and exercise. Both HGS and 6MWT have previously been used in assessments of frail elderly patients [44, 45]. The tests are performed at baseline and not at follow-up and are only conducted on patients in the intervention group as part of the CGA and care intervention.*Nutrition*, malnutrition is common in the elderly population, especially if hospitalized, living in nursing facility or having home help services. Malnutrition is often unrecognized if not specifically targeted. The Mini-Nutritional Assessment-Short Form (MNA-SF) is a validated instrument for nutritional screening in frail elderly individuals. It renders a score which places the patients in one of three groups: normal nutritional status, at risk of malnutrition or malnourished [46, 47]. A clinically significant change is defined as a change in group classification. The patients in the intervention group are screened by a dietician at baseline and by a ward nurse or a dietician at the day of/day before surgery. The patients in the control group are screened by a study nurse at both measurements.*Medication safety*, polypharmacy and the use of potentially inappropriate medications is a growing issue in the elderly population. There is often a need of reviewing and altering an elderly individual’s prescribed medications to reduce the risk of adverse drug reactions and to enable beneficial pharmacological treatments [48–50]. The Safe Medication Assessment (SMA), including a review of the current list of medications [51], is used as a basis for assessing the individual patient’s medications in the trial. The instrument renders a score of 0–30, where a higher score indicates a safer treatment. A clinically significant change is defined as a shift of minimum 1 point in either direction. The questionnaire is filled out by a study nurse at baseline and at revisit, for all participants. To identify adverse drug reactions (ADRs), underuse of evidence-based drug therapy and effects of inappropriate medications, scoring scales [49, 50] and clinical judgements based on medical records will be used. These judgements will be retrospectively performed by senior clinicians [52].*Cognition*, a decline in cognitive function is naturally present in the ageing process. Some elderly individuals are experiencing a more pronounced decline, resulting in cognitive impairment or dementia [53]. In the trial, the Mini-Mental State Examination (MMSE) is used as a screening instrument of cognitive function at baseline. It is a validated and reliable assessment tool in screening for cognitive impairment [54]. The screening is performed by a study nurse at baseline for all participants, but the measurement is not done at follow-up.*Frailty* is an independent risk factor of adverse health outcomes and death [21] and also a predictor of increased hospital and health care costs [25]. The degree of frailty is assessed using the Clinical Frailty Scale (CFS-9). The scale ranges from 1, “very fit”, to 9, “terminally ill”. The scale has been validated and proven to be of prognostic value in clinical practice [26, 55, 56]. The estimates are performed by a study nurse at baseline and at revisit, for all participants. A clinically relevant change is defined as a shift of minimum 1 step on the scale. During the initial phase of the trial’s recruitment, a revision of the CFS-9 scale was made, including minor adjustments in the description of the different levels of frailty [57]. Before the updated version (v 2.0) was put into use, a new application to the Swedish Ethical Review Authority was made and was approved on 2021-05-31.*Complications*, postoperative complications are common in elderly patients undergoing colorectal cancer surgery. The complications can result in additional treatments, reoperations, the need of intensive care and death [7, 8]. The Clavien-Dindo classification is a validated and clinically relevant instrument for identifying and grading adverse postoperative events [58]. The postoperative complications are assessed by a physician based on data from the medical records at the time of revisit, for all participants.*Comorbidity*, the patient’s comorbidity is valued through the Charlson comorbidity index (CCI). The instrument is used to assess the total burden of disease and predicts a 10-year mortality for a patient, by using 19 categories of comorbidities. Each condition is given a grade of 1, 2, 3 or 6, based on the risk of death associated with the specific comorbidity [59, 60]. The CCI index estimate will be performed by a physician, based on data from the medical records at baseline and at revisit, for all participants.*Health-related quality of life (HRQoL)*. The instrument EuroQoL-5D-5L (EQ-5D-5L) is used to assess HRQoL in the trial. The tool consists of a questionnaire containing five health dimensions with five response levels and of a visual analogue scale (VAS) where the patient estimates their own overall current health. Each estimated score is represented by an index value which is derived from a pre-defined value set [61, 62]. The assessments are overseen by a study nurse at baseline and at follow-up (2 and 12 months), for all participants.*Health economical calculations*. A health care system perspective will be applied including hospital and primary care. Cost-effectiveness will be analysed based on mortality and HRQoL data (quality-adjusted life years [QALYs]) and costs of hospital care and primary care at baseline, 2 and 12 months post-surgery. An incremental cost-effectiveness ratio (ICER) is calculated regarding cost/QALY gained. QALYs are calculated by multiplying the health state value with the patient’s survival time at 12 months; see also the “Statistical methods for primary and secondary outcomes” section. Data regarding health care costs will be collected and documented for all participants at 2 months and 12 months from baseline. Hospital costs will be obtained from the Swedish Cost-per-Patient database [63] and from hospital-specific administrative systems. Primary health care costs will be collected from the administrative regional health care database in Västra Götalandregion (VEGA) [64] and by the use of models and actual health care contacts.*Mortality*, mortality data will be extracted from patient medical records and cross-checked against the Swedish Population Registry regarding all participants at 2, 3 and 12 months from baseline.

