## Statistical methods

### Statistical methods for primary and secondary outcomes {20a}

The primary analysis will be performed according to “intention to treat”. As a secondary analysis, a per-protocol analysis will be made. The dataset will be closed, an analysis plan will be made and a multivariate analysis with relevant confounding factors will be performed.

QALYs are calculated by multiplying the health care state with the patient’s survival time at 12 months. The HRQoL is considered linear between 2 values (index and 12-month follow-up). If a person dies during follow-up, the HRQoL at index is carried forward to the time of death. If only HRQoL at index is available (missing data at the 12-month follow-up), the score is carried forward, and, conversely, if only the 12-month follow-up score is available (i.e. data missing at index), this score is carried backward to the index. If a person dies during the index care episode, the QALY is set to 0. Adjusted data regarding costs and effects might be used in the cost-effectiveness analysis. Adjustments are done for age, sex and CCI.

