### Methods in analysis to handle protocol non-adherence and any statistical methods to handle missing data {20c}

The intention-to-treat (ITT) principle will be applied.

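### Ending data registration after deviation, missed follow-up or discontinuation contradicts the intention-to-treat analysis; the primary endpoint is exposed only through patients who discontinue

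*Protocol article*

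**What the plan says.** The protocol article, under Plans to promote participant retention and complete follow-up {18b}, sets two rules.

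- Deviators and non-attenders: "Participants who deviate from the protocol or fail to appear at follow-up will be checked against the mortality registry but not further registered".
- Patients who leave: "Participants who choose to discontinue their participation in the trial will be registered in a log and no further measurements or registrations will be made". No mortality check is mentioned for them.

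Other sections say something different.

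- Statistical methods {20a} makes intention to treat (ITT) the primary analysis and per-protocol a secondary one. Section {20b} repeats ITT. Section {20c}, the item on non-adherence and missing data, reads in full: "The intention-to-treat (ITT) principle will be applied".
- The primary endpoint in Outcomes {12} is "All-cause 90-day mortality". Under Outcomes and measurements, mortality is taken from medical records and "cross-checked against the Swedish Population Registry regarding all participants at 2, 3 and 12 months from baseline".
- The same section covers hospital stay, discharge destination and "30-day readmission rates for all participants is collected from patient medical records". Complications are graded by a physician from the medical records, again for everyone. Costs come from a national cost database, hospital administrative systems and a regional care database.
- Confidentiality {27} separately lets participants have their data retracted, deleted or restricted at any time.

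**The concern.** ITT needs outcome data on every randomised patient, whatever happens afterwards. Deviation, non-attendance and discontinuation are all events after randomisation. A rule that ends data collection when they occur decides who can be analysed by something the allocation may influence. Calling the analysis ITT does not recover data that were never registered, and neither does a later analysis plan.

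The rule on deviation is the clearest fault. A deviator has withdrawn nothing, may still attend, and still has a hospital record. The Discussion expects that differing hospital routines may require deviations, so a patient could lose registration because of something the site did.

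What is at stake is the comparison on stay, readmission, discharge destination, complications and costs. For discontinuers, it is also the primary endpoint.

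**Working it through.** **Step 1. What {18b} leaves for each group, read literally**

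| After randomisation | Mortality | Record- and database-based outcomes (stay, discharge, readmission, complications, costs) | Visit-based outcomes (ADL, medication assessment, CFS-9, EQ-5D-5L) |
|---|---|---|---|
| Adheres and attends | kept | kept | kept |
| Deviates | kept | ended | ended, even if the patient attends |
| Misses follow-up | kept | ended | missing for that visit in any case |
| Chooses to discontinue | apparently ended | ended | ended |

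The third column is the avoidable loss. Section {18a} has stay, readmission, discharge destination and complications documented on forms at baseline and the postoperative visit, but Outcomes and measurements sources them from records. A missed visit therefore removes nothing that the record does not hold. The last row conflicts with the mortality cross-check for all participants.

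**Step 2. The plan's own figure**

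Inputs from Sample size {14}: 15% versus 5%, 80% power, alpha 0.05 (two-sided assumed, since sidedness is not stated), 5% loss, 170 per group.

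- n = [1.960·√(2·0.10·0.90) + 0.842·√(0.15·0.85 + 0.05·0.95)]² / 0.10² gives 141 per group.
- With continuity correction: 160.
- 160 / 0.95 gives 169, against 170 stated. The figure is reproduced.

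Pooled normal-approximation power, without continuity correction, is 0.871 at 170 per group and 0.852 at 161 (170 less 5%). A 5% loss costs little power, so the issue is bias.

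**Step 3. Primary endpoint: discontinuers only**

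Let p be true mortality in an arm, w the share lost, and r the risk of those lost relative to the arm. Observed mortality = (p − w·r·p) / (1 − w).

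Assumed, not from the documents: no true effect, p = 0.15 in both arms, and the shares lost below.

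| Lost, intervention / control | r | Observed, intervention / control | Spurious benefit | Rejection rate (nominal 5%) |
|---|---|---|---|---|
| 5% / 5% | 3 | 13.4% / 13.4% | 0 | not computed |
| 8% / 2% | 1 | 15.0% / 15.0% | 0 | not computed |
| 8% / 2% | 2 | 13.7% / 14.7% | 1.0 point | 5.7% |
| 8% / 2% | 3 | 12.4% / 14.4% | 2.0 points | 8.2% |
| 10% / 0% | 2 | 13.3% / 15.0% | 1.7 points | 7.1% |
| 10% / 0% | 3 | 11.7% / 15.0% | 3.3 points | 14.0% |

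Swapping the arms reverses the sign. For deviators and non-attenders the loss on mortality is zero.

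**Step 4. A record-based secondary outcome, for example any complication**

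Within an arm, the registered rate differs from the true rate by −w·Δ, where Δ is the rate in those lost minus the rate in those registered. The error in the difference (control minus intervention) is w_I·Δ_I − w_C·Δ_C. All inputs below are assumed.

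- Intervention loses 15% at 50% against 30% in the rest; control loses none: true rate 0.15·0.50 + 0.85·0.30 = 33%, registered 30%, error 3 points.
- Intervention loses 25% at 60% against 30%; control loses none: 0.25·0.60 + 0.75·0.30 = 37.5%, registered 30%, error 7.5 points.
- Both arms lose 15% with Δ = 20 points: 3 − 3 = 0.
- Intervention loses 15% and control 25%, both with Δ = 20 points: 3 − 5 = −2 points, against the intervention.
- Δ = 0 in both arms: 0 for any loss.

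The documents do not say which case applies.

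**The case against.** The strongest reply has four parts.

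- **Primary endpoint.** A reader might infer that ITT on 90-day mortality fails for all three groups. It does not. Deviators and non-attenders keep the mortality check, which also protects 1-year mortality, itself a secondary endpoint. So it is wrong to say that every secondary outcome is affected. This stands.
- **Discontinuers.** Stopping collection for someone who leaves the trial can reflect consent, and {27} gives participants that right. This stands in part. Section {18b} does not separate leaving visits or the intervention from refusing use of records, and Outcomes and measurements still promises mortality for all participants.
- **Direction of bias.** A reader might infer that the rule removes the sickest patients, more so from the intervention arm, and so favours the intervention. Only that arm has individual recommendations with weekly adherence review, so unequal loss is plausible. But no deviation or attendance rates are given. Ending the intervention early under {11b} is a step the protocol itself provides, and {18b} does not say whether it counts as deviation. The one source of deviations named, differing hospital routines, is not specific to an arm. The objection stands: the inference is possible but undocumented.
- **A separate per-protocol analysis and carried-forward quality of life.** Planning both analyses suggests that deviators were meant to stay in the ITT set, and the QALY rule retains patients without a 12-month score. That shows intent. It does not supply the unregistered complications, readmissions or costs.

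**Conclusion.** The contradiction is established from the text alone. Section {18b} ends registration of non-mortality outcomes for deviators and non-attenders, and of all outcomes, apparently including mortality, for discontinuers. This conflicts with ITT in {20a}, {20b} and {20c}, and with record- or registry-based collection for all participants under Outcomes and measurements.

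The consequence is limited but real. Non-mortality secondary outcomes would be compared on a set selected after randomisation. The primary endpoint is exposed only through discontinuers, whose number is not given.

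The size and direction of bias are unknown. It is zero if loss is equal between arms and of the same risk, or if those lost have average risk. Under the assumed unequal, high-risk losses it is about 1 to 3 points on mortality, and 3 to 7.5 points on a complication rate when only the intervention arm loses patients. These figures are illustrations, not estimates for this trial.

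A reader might also set the 5% loss allowance (0.05·340 = 17 patients) against the deaths expected under the design (0.15·170 + 0.05·170 = 34). The documents do not support that comparison: the 5% is general loss to follow-up, not loss of vital status.

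**What to change.** Reword {18b} and bring it into line with {20a}–{20c} and Outcomes and measurements:

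1. Deviation, non-attendance or stopping the intervention does not end data collection.
2. For every randomised patient, mortality, length of stay, readmission, discharge destination, complications and costs continue to be collected from records, registries and databases.
3. Record and registry collection stops only when a patient explicitly withdraws consent to data use, by the route in {27}. That is logged as its own category, separate from stopping the intervention or visits.
4. State whether early ending of the intervention under {11b} counts as a deviation, so that sites classify patients alike.

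The cost is extra chart review for patients now dropped, an amendment, and consent-form wording. The data sources are already in use and the sample size does not change. Recruitment {15} reports about 50 of 340 patients included, so a change at that stage would cover roughly 290 from the start. For those already enrolled, the consent they gave should be checked before collection is extended.
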